## Abstract

**Background:** Diastasis rectus abdominis (DRA) is one of the common complications during pregnancy and post-partum, which has psychological and physical effects on post-partum women. Acupuncture, a worldwide alternative therapy, has attracted wide attention in preventing and treating diseases related to pregnancy and childbirth. This study aims to evaluate the efficacy of acupuncture combined with physical training in treating post-partum rectus muscle dissociation.

**Methods:** This is a randomized, controlled trial of DRA in post-partum conducted at Hangzhou Hospital of Traditional Chinese Medicine Affiliated with Zhejiang University of Chinese Medicine. The primary purpose is to evaluate the effectiveness of acupuncture and physical training on DRA in post-partum women. The study will be conducted from March 2022 to March 2023. The acupuncture group received acupuncture and physical training (*n* = 48), the sham acupuncture group received sham acupuncture and physical training (*n* = 48), and the physical training group received physical training (*n* = 48). These experiments perform once/day, five times a week for 2 weeks, followed up for half a year after the end of the course of treatment. Our tests perform a course of treatment, which includes a total of 10 consecutive treatments. Furthermore, the patient will be followed up for half a year after the treatment. Primary and secondary indicators, including inter recti distance (IRD), linea alba (LA) tension, the MOS item short-form health survey (SF-36), short-form McGill pain questionnaire-2 (SF-MPQ-2), body mass index (BMI), waist-to-hip ratio (WHR), leeds dyspepsia questionnaire (LDQ), menstrual distress questionnaire (MDQ), 10 items of edinburgh post-natal depression scale (EPDS-10), the modified body self-image scale (MBIS), international consultation incontinence questionnaire short-form (ICIQ-SF) and hernia-related quality-of-life survey (HerQles), which will be evaluated before and after treatment and half a year after treatment. Adverse events and side effects during each treatment will be collected and recorded.

**Discussion:** There is evidence that acupuncture and physical training can treat DRA in post-partum. In this study, we evaluate the effectiveness of acupuncture in post-partum with DRA.

## Highlights

- Between 35 and 70% of post-partum rectus muscle dissections fail to recover without any treatment or exercise.- This paper presents a treatment method for post-partum rectus abdominal separation.- Acupuncture for post-partum rectus separation as a technique of internal rectus stimulation.

## Background

Diastasis recti abdominis is a condition in which both rectus abdominal muscles disintegrate to the sides, accompanied by the extension of the linea alba tissue and bulging of the abdominal wall (1). 30–70% of pregnant women develop DRA during pregnancy (2). Between 35 and 70 percent of pregnant women do not recover after giving birth without treatment or exercise (3). In addition, 39% to 45% of women still have DRA at 6 months post-partum, and the incidence of DRA at 1 year post-partum is 23–32% (1). DRA has both psychological and physical effects on post-partum women. Women with DRA primarily receive the application of support band and abdominal band during pregnancy and post-partum (4), electrical stimulation, surgical repair (5), and physical training (6). There is a lack of unified and effective treatment, and there are few studies on the efficacy and safety of DRA physical training (5, 7). As a worldwide alternative therapy, acupuncture has received wide attention in preventing and treating diseases related to pregnancy and childbirth.

Acupuncture combined with physical training can significantly improve tissue excitability, which improves blood circulation and systolic muscle function (8) and adjust the mechanical balance of the post-partum abdominal muscle group. In abdominal physical training, the increase of abdominal pressure makes the pelvic floor vulnerable to adverse effects and causes or exacerbates pelvic floor dysfunction. Acupuncture can well cause the secondary synergism of pelvic floor muscles by activating the transverse abdomens (9, 10).

However, the long-term efficacy is still unclear, and there is a lack of solid objective evidence. To date, no RCT studies the impact of acupuncture on DRA or evaluates the standardized application of DRA by acupuncture. This study comprehensively evaluates the effectiveness and safety of acupuncture in the treatment of post-partum DRA, the effective, and safety of DRA physical training. It provides a reference for clinical treatment of post-partum DRA.

### Hypothesis

The hypothesis is that intervention with acupuncture is better than physical training in these outcomes of the inter recti distance (IRD) of DRA. We also expect to prove that acupuncture can be an ideal safe and conservative alternative for patients with DRA who fail in conventional physiotherapy.

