### Participants and Recruitment

The study was conducted from March 2022 to March 2023. The acupuncture group received acupuncture and physical training (*n* = 48), the sham acupuncture group received sham acupuncture and physical training (*n* = 48), and the physical training group received physical training (*n* = 48).

Participants were recruited from inclusion criteria:

(1) A female aged 18–45 years with no previous history of pathological rectus abdominal dissection;(2) Vaginal delivery, 42 days to 1 year post-partum;(3) DRA diagnostic criteria:The patient should keep in the supine position, with knees bending about 90°, the whole body relaxed, and the soles of the feet flat. The examiner shall put the abdomen of one hand finger on the umbilical level of the patient;The patient is told to breathe through the abdomen and to lift one's head and shoulders slightly off the bed;

Measuring the width of the finger inserted by the examiner, DRA is diagnosed when IRD ≥ 2 cm (14–16).

(4) No cognitive barriers, able to understand and communicate correctly;(5) Have not received treatment for DRA in other hospitals or institutions;(6) Those who sign the informed consent cooperate with the treatment and can adhere to the completion of all treatment as planned.

Patients who meet the above six criteria can be included in this study.

The subjects studied for DRA in post-partum women should follow the following exclusion criteria:

(1) One is suspected or diagnosed with severe spinal lesions (such as spinal fractures, metastases, inflammatory or infectious diseases, cauda equina syndrome/widespread neurological disease) and neurological injury;(2) One has motor contraindications or severe infectious diseases such as fractures, severe heart disease, hypertension, cancer;(3) Any plans for surgery soon;(4) History of cesarean section;(5) Abdominal operation history;(6) Any of the above shall be excluded.

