### Randomization and Binding

A total of 144 eligible patients were recruited and randomly assigned at a 1:1:1 ratio to receive acupuncture treatment or sham acupuncture treatment or be placed on a physical training. Central randomization, using an online or messaging system, was performed by the Brightech Magnsoft Data Services. The randomization sequence was generated in blocks of varying sizes and stratified by centers.

The acupuncture and sham acupuncture groups were blinded, while those in the physical training group were not. All clinical examinations were performed by [name] and [name] physiotherapists blinded to data collected through the questionnaire. Due to iodophor disinfection traces in the abdomen after electroacupuncture, the therapists knew the groups, so [name] performed electroacupuncture treatment after rehabilitation exercise first. All the therapists did not know the purpose of the experiment.

The acupuncture and sham acupuncture groups were blinded, while those in the physical training group were not. All clinical examinations were performed by [name] and [name], two physiotherapists blinded to data collected. Due to iodophor disinfection traces in the abdomen after electroacupuncture, the therapists knew the groups. So [name] performed electroacupuncture treatment after rehabilitation exercise first. Outcome assessors, data collectors, and statisticians did not know the purpose of the experiment and were blinded to the treatment allocation.

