## Discussion

There is evidence that physical training can improve DRA (13, 23). To date, however, previous research focuses on how to reduce IRD for DRA treatment (24) but ignores its safety and effectiveness on physiological, psychological, and other systemic regulation. In the process of DRA exercise rehabilitation, individual differences in proprioception of abdominal wall and pelvic floor and cooperative motor control ability should be considered, and patient education and self-perception ability training should be paid attention to. At present, there are no published data on the effectiveness of acupuncture in post-partum with Diastasis Recti Abdominis by A Randomized Controlled Clinical Trial Study.

Increasing adherence to self-care is a challenge in diseases such as DRA. An acupuncture-based intervention to replace single physical training may improve DRA in the future. This study aims to evaluate the effectiveness and safety of acupuncture in post-partum with Diastasis Recti Abdominis to bring the gospel to most DRA patients.

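### The hypothesis is worded as acupuncture against physical training, and as an option after failed physiotherapy, but the design tests only acupuncture added to training in women not selected for failure

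*Protocol article*

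**What the plan says.** The protocol article, under Hypothesis, makes two statements. The first is comparative: "The hypothesis is that intervention with acupuncture is better than physical training in these outcomes of the inter recti distance (IRD) of DRA". The second is an expectation of proof that "acupuncture can be an ideal safe and conservative alternative for patients with DRA who fail in conventional physiotherapy".

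The arms are defined in the Abstract and again under Participants and Recruitment, with 48 women in each:

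- "The acupuncture group received acupuncture and physical training"
- "the sham acupuncture group received sham acupuncture and physical training"
- "the physical training group received physical training"

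The section on randomisation uses shorter labels and leaves out the shared training: women are "randomly assigned at a 1:1:1 ratio to receive acupuncture treatment or sham acupuncture treatment or be placed on a physical training".

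On earlier treatment, inclusion criterion 5 reads: "Have not received treatment for DRA in other hospitals or institutions". No inclusion or exclusion criterion mentions failure of, or inadequate response to, physiotherapy.

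The Discussion looks ahead as follows: "An acupuncture-based intervention to replace single physical training may improve DRA in the future".

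**The concern.** The hypothesis fixes what a positive result will be taken to show. Read literally, a significant difference in IRD would be reported as acupuncture outperforming exercise, and as support for using it where exercise has failed. The trial cannot supply evidence for either statement: every participant trains, and nobody is enrolled because training failed. A reader could conclude that training may be dropped, on data from women who all received it.

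The hypothesis also names only the training arm as comparator, and that arm is not blinded. The sham arm, a third of the participants (48 of 144), does not appear in it. A difference from training alone combines needling with expectation and added session time. Only the sham contrast separates these.

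**Working it through.** **Step 1. Hypothesis against design.**

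| Element | What the Hypothesis needs | What the protocol article provides |
|---|---|---|
| Intervention in statement 1 | Acupuncture | Acupuncture plus training (Abstract; Participants and Recruitment) |
| Comparator in statement 1 | Physical training | Training alone, and sham plus training |
| Contrast in statement 1 | Acupuncture against training | (A + T) against T, and (A + T) against (S + T) |
| Population in statement 2 | Women in whom physiotherapy failed | Not selected by any criterion; criterion 5 requires no treatment for DRA elsewhere |
| Role in statement 2 | Acupuncture as an alternative | No arm has acupuncture without training |

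Here A is acupuncture, S is sham and T is training. T is in every arm, so both contrasts give the effect of A (or of A over S) in the presence of T. Neither gives A against T.

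Criterion 5 does not literally bar women treated earlier at the trial hospital. Even so, nothing selects or identifies them as treatment failures, so statement 2 has no defined population.

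**Step 2. What the sample size rests on.** Inputs from the Sample Size section: mean IRD 2.09 for training and 1.43 for acupuncture plus training (no unit given there), alpha 0.05 two-sided, power 0.90, effect size 0.313249, 43 per group, 10% loss, 48 per group.

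Assumption: 0.313249 is Cohen's f for a one-way comparison of three groups. With noncentrality 3n × f²:

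- n = 43: 129 × 0.098125 = 12.66, power 0.893
- n = 44: power 0.89999
- n = 45: power 0.907

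The stated 43 is thus reproduced to within two women per group. For loss, 43 / 0.90 = 47.8, rounded up to 48, and 3 × 48 = 144, as stated. The size therefore belongs to the add-on question: 2.09 − 1.43 = 0.66 is the expected difference between A + T and T.

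**Step 3. Is the sham contrast covered?** No mean for sham and no SD are given. Under the same reading of f, the SD follows once a sham mean is assumed: SD = σₘ / f, where σₘ is the root mean squared deviation of the three group means from their average.

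- Sham equal to training (1.43, 2.09, 2.09): σₘ = 0.3111, SD = 0.3111 / 0.313249 = 0.993. Acupuncture against sham: d = 0.66 / 0.993 = 0.665. With 43 per group, the noncentrality is 0.665 × √(43/2) = 3.08 and two-sided t-test power is about 86%.
- Sham midway (1.43, 1.76, 2.09): σₘ = 0.2694, SD = 0.860. Acupuncture against sham: d = 0.33 / 0.860 = 0.384. The noncentrality is 1.78 and power is about 42%.

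Both figures are for a single unadjusted pairwise test at 0.05, without the gain from baseline adjustment in the planned model.

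**The case against.** The strongest reply is that the first statement is shorthand. The section on randomisation also calls the combined arm simply acupuncture, while the Abstract's aim, the arm definitions and the sample size all describe the combination. Read that way, statement 1 is the very contrast the trial is sized for. This stands in part: a reader might infer that the trial has no testable hypothesis or that its comparison is invalid, and the document does not support that. The add-on hypothesis is testable. The reply does not rescue statement 2, which has no population on any reading and speaks of an alternative.

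Four further inferences should be resisted.

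- *The Discussion claims that acupuncture can replace training.* The sentence is a hedged outlook, and replacing training given singly may mean replacing it with the combination. It needs clarifying; it is not a second objective.
- *The acupuncture and sham arms get five hours more hands-on contact.* The Intervention section gives 30 minutes per session, and the Abstract gives 10 sessions, so 10 × 30 = 300 minutes of added session time. How much of that is hands-on is not stated.
- *The IRD result is distorted by expectation.* IRD is measured by ultrasound, and outcome assessors are described as blinded to allocation. The concern about reported symptoms applies to the questionnaires, which the hypothesis does not name.
- *Every efficacy claim must rest on the sham contrast, and this is only a change of wording.* Making that contrast decisive would change the key comparison, and its power is unknown (42% to 86% across the two cases shown). The sham arm is in the design and treatment arm is in the planned model, so the contrast can be estimated. Its formal ranking may be set in a fuller document that is not shown.

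**Conclusion.** The point holds as a mismatch between the stated hypothesis and the design. No participant receives acupuncture without training, and none is selected for failed physiotherapy, so the trial supports neither superiority over training nor use after its failure. It can support an add-on effect on IRD, the planned difference being 0.66. A difference from the unblinded training arm shows the total add-on effect (needling plus expectation and added session time). Attribution to needling needs the sham contrast, for which the document gives no expected mean.

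The mismatch rests on the text alone. The power range rests on reading 0.313249 as Cohen's f and on two assumed sham means. This should be fixed: it changes what may be concluded, but not the validity of the randomised comparison.

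**What to change.** 1. Replace the first statement of the Hypothesis with: acupuncture plus physical training gives lower IRD than (a) physical training alone, the total add-on effect, and (b) sham acupuncture plus physical training, the effect of needling.
2. Delete the claim about women in whom conventional physiotherapy has failed.
3. Reword the Discussion sentence so that it refers to adding acupuncture to training and does not suggest giving it instead.
4. State that (a) alone does not attribute a difference to needling and that such attribution needs (b). Add that the Sample Size section gives no mean for sham, so power for (b) is not established.

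The cost is a narrower claim and a few sentences of text. Arms, eligibility and sample size do not change. If the sponsor went further and made (b) the decisive comparison, that would be a separate decision requiring an assumed sham mean and SD.

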## Methods

This study protocol was developed under the Recommendations for Interventional Trials 2013 Statement (SPIRIT 2013) (11) (Table 1) and the Consolidated Reporting Trials statement (CONSORT 2010) when applicable (12).

**Table 1 T1:** SPIRIT 2013 checklist: recommended items to address in a clinical trial protocol and related documents^*^.

**Section/item**	**Item no**.	**Description**	**Yes/No**
**Administrative information**			
Title	1	Descriptive title identifying the study design, population, interventions, and, if applicable, trial acronym	Yes
Trial registration	2a	Trial identifier and registry name. If not yet registered, name of intended registry	Yes
	2b	All items from the World Health Organization Trial Registration Data Set	Yes
Protocol version	3	Date and version identifier	Yes
Funding	4	Sources and types of financial, material, and other support	Yes
Roles and responsibilities	5a	Names, affiliations, and roles of protocol contributors	Yes
	5b	Name and contact information for the trial sponsor	Yes
	5c	Role of study sponsor and funders, if any, in study design; collection, management, analysis, and interpretation of data; writing of the report; and the decision to submit the report for publication, including whether they will have ultimate authority over any of these activities	Yes
	5d	Composition, roles, and responsibilities of the coordinating center, steering committee, endpoint adjudication committee, data management team, and other individuals or groups overseeing the trial, if applicable (see Item 21a for data monitoring committee)	Yes
**Introduction**			
Background and rationale	6a	Description of research question and justification for undertaking the trial, including summary of relevant studies (published and unpublished) examining benefits and harms for each intervention	Yes
	6b	Explanation for choice of comparators	Yes
Objectives	7	Specific objectives or hypotheses	Yes
Trial design	8	Description of trial design including type of trial (e.g., parallel group, crossover, factorial, single group), allocation ratio, and framework (eg, superiority, equivalence, non-inferiority, exploratory)	Yes
**Methods: participants, interventions, and outcomes**			
Study setting	9	Description of study settings (eg, community clinic, academic hospital) and list of countries where data will be collected. Reference to where list of study sites can be obtained	Yes
Eligibility criteria	10	Inclusion and exclusion criteria for participants. If applicable, eligibility criteria for study centers and individuals who will perform the interventions (eg, surgeons, psychotherapists)	Yes
Interventions	11a	Interventions for each group with sufficient detail to allow replication, including how and when they will be administered	Yes
	11b	Criteria for discontinuing or modifying allocated interventions for a given trial participant (eg, drug dose change in response to harms, participant request, or improving/worsening disease)	Yes
	11c	Strategies to improve adherence to intervention protocols, and any procedures for monitoring adherence (eg, drug tablet return, laboratory tests)	Yes
	11d	Relevant concomitant care and interventions that are permitted or prohibited during the trial	Yes
Outcomes	12	Primary, secondary, and other outcomes, including the specific measurement variable (eg, systolic blood pressure), analysis metric (eg, change from baseline, final value, time to event), method of aggregation (eg, median, proportion), and time point for each outcome. Explanation of the clinical relevance of chosen efficacy and harm outcomes is strongly recommended	Yes
Participant timeline	13	Time schedule of enrolment, interventions (including any run-ins and washouts), assessments, and visits for participants. A schematic diagram is highly recommended (see Figure)	Yes
Sample size	14	Estimated number of participants needed to achieve study objectives and how it was determined, including clinical and statistical assumptions supporting any sample size calculations	Yes
Recruitment	15	Strategies for achieving adequate participant enrolment to reach target sample size	Yes
**Methods: assignment of interventions (for controlled trials)**			
Allocation:			Yes
Sequence generation	16a	Method of generating the allocation sequence (eg, computer-generated random numbers), and list of any factors for stratification. To reduce predictability of a random sequence, details of any planned restriction (eg, blocking) should be provided in a separate document that is unavailable to those who enroll participants or assign interventions	Yes
Allocation concealment mechanism	16b	Mechanism of implementing the allocation sequence (eg, central telephone; sequentially numbered, opaque, sealed envelopes), describing any steps to conceal the sequence until interventions are assigned	Yes
Implementation	16c	Who will generate the allocation sequence, who will enroll participants, and who will assign participants to interventions	Yes
Blinding (masking)	17a	Who will be blinded after assignment to interventions (eg, trial participants, care providers, outcome assessors, data analysts), and how	Yes
	17b	If blinded, circumstances under which unblinding is permissible, and procedure for revealing a participant's allocated intervention during the trial	Yes
**Methods: data collection, management, and analysis**			
Data collection methods	18a	Plans for assessment and collection of outcome, baseline, and other trial data, including any related processes to promote data quality (eg, duplicate measurements, training of assessors) and a description of study instruments (eg, questionnaires, laboratory tests) along with their reliability and validity, if known. Reference to where data collection forms can be found, if not in the protocol	Yes
	18b	Plans to promote participant retention and complete follow-up, including list of any outcome data to be collected for participants who discontinue or deviate from intervention protocols	Yes
Data management	19	Plans for data entry, coding, security, and storage, including any related processes to promote data quality (eg, double data entry; range checks for data values). Reference to where details of data management procedures can be found, if not in the protocol	Yes
Statistical methods	20a	Statistical methods for analyzing primary and secondary outcomes. Reference to where other details of the statistical analysis plan can be found, if not in the protocol	Yes
	20b	Methods for any additional analyses (eg, subgroup and adjusted analyses)	Yes
	20c	Definition of analysis population relating to protocol non-adherence (eg, as randomized analysis), and any statistical methods to handle missing data (eg, multiple imputation)	Yes
